### 2.11. Data Management

Data collection will be conducted using an electronic data capture (EDC) system (Vanderbilt University, TN), called REDCap. All participating study sites will be granted access to REDCap, with access controls implemented via IP address restrictions to ensure secure and authorised use. Data entry and any corrections will be restricted to site personnel who have completed GCP training and have been formally authorised by the principal investigator.

Upon enrolment in the study, each participant will be assigned a unique study number or “participant ID” within the REDCap system, ensuring pseudonymisation. In all documentation to which the coordinating centre, sponsor, or Chief Investigator (CI) has access, this number will solely identify participants. The list that matches these participant IDs to the participants’ names is safeguarded by the local site. Any personal identifiers will not be recorded in the study database (REDCap).

All entries in the eCRFs must fully align with the corresponding source data. In instances where data are unavailable or unknown, this must be explicitly documented within the eCRF. The eCRFs are designed to capture all variables specified by the study protocol (see Supplementary Materials Section SC). Data quality and consistency will be systematically reviewed by qualified personnel, including clinical research monitors and data managers, with any discrepancies subject to query and resolution in accordance with standard data management procedures.

Users are limited to viewing data pertaining only to participants enrolled at their respective study sites. All user activity within the REDCap system is automatically recorded and traceable via comprehensive audit trails and log files, ensuring transparency and accountability.

### 2.12. Ethics Approval

The finalized and operational study protocol was approved by the Medical Ethics Committee of all participating centres, and final approval was obtained by the Central Medical Ethics Committee of UZ Brussel/VUB on 3 July 2024 (23435_REMOTE). This study was registered with ClinicalTirals.gov (https://clinicaltrials.gov/study/NCT06175208) on 8 December 2023 [31].

## 3. Results

The initiation visits for the REMOTE study took place between September and December 2024 in all twelve participating centres. The first patient was randomised on 16 October 2024. The number of participants currently stands at 82 of the target 339 on 31 July 2025.

## 4. Discussion

The aim of this study is to examine the efficacy of iEFT and iMMI in alleviating FCR, one of the most frequently reported psychosocial problems by cancer survivors. Based on the outcomes of the former EMOTICON trial [32], it is expected that iEFT may control and diminish FCR experienced by cancer survivors. The integration of exposure therapy, cognitive framing, and acupressure [15] renders EFT a straightforward yet effective tool to manage negative thoughts. Furthermore, it is a patient-friendly intervention that can be easily delivered remotely.

For the active control arm in the study, iMMI, it is expected that this intervention arm will also be able to reduce FCR. In addition, this intervention group may offer novel insights into the impact of this particular mindfulness approach on FCR and on the overall psychological well-being of cancer survivors.

One of the potential limitations related to the type of intervention and topic of the trial assumes a potential selection bias for white, highly educated, female participants. However, the research group consciously decided to include all cancer types as all cancer survivors may cope with (severe) levels of FCR. We have anticipated by including the biggest risk factors for selection bias (age, gender), which are also related to higher levels of FCR, as stratification variables. Hereby, the intervention arms should all contain equal distribution of younger/older and male/female participants. Race and ethnicity are not taken into consideration, and this may potentially be a topic for the final discussion together with the general analysis of the demographic data.

Another limitation could be the entire online format, which increases the risk for drop-out. We may anticipate this by keeping close contact with local trial coordinators in the first place, stressing the importance of the eligibility criteria, but even more the importance of the motivation of participants. Next, it is the central coordinator’s responsibility to follow up on all participants and the response to the online questionnaires via MyNexuzHealth.

Positive outcomes may promote the integration of iEFT and iMMI into clinical practice. Therefore, the time toxicity of both interventions is measured as this may significantly impact the feasibility of implementation.

## 5. Conclusions

In conclusion, this pragmatic RCT is of great importance given the considerable need and demand from cancer survivors for effective strategies to manage FCR [9]. Identifying a low-threshold, cost-effective intervention could have a substantial impact on the survivorship trajectory and enhance the overall experience of this expanding population. Moreover, the internet-based delivery of the interventions may facilitate an effective and scalable implementation in routine clinical practice, the ultimate objective of this research. The involvement of the national scientific societies, such as the BGOG and BSMO, will be helpful in facilitating this potential implementation in clinical practice. In addition, their involvement can also help to promote integration into international guidelines, so that every patient coping with FCR can have access to this form of supportive cancer care.

## 6. Trial Status

The protocol number is 2345_REMOTE and concerns version 2.0 (dd. 1 July 2024). Recruitment started in October 2024 and is projected to be finished in March 2027.

## Figures and Tables

**Figure 1 brainsci-15-00900-f001:**
[figure not shown]
Diagram of planned study flow.

**Figure 2 brainsci-15-00900-f002:**
[figure not shown]
Head, torso, and hand acupressure points involved in the application of EFT (Figure adapted from Church et al. [29]). The process starts with a ‘Setup Statement’ while performing acupoint tapping on the side of the hand. For the remainder of the process, patients gently tap with two fingers on head and torso points while repeating the ‘Reminder Phrase’.

**Table 1 brainsci-15-00900-t001:** Secondary and tertiary objectives.

Secondary objectives
• Explore whether iEFT is more effective than iMMI for improving FCR
• Compare the efficacy of the two interventions relative to a WLC group on distress, QoL and health status
• Explore whether iEFT is more effective than iMMI (active control condition) for improving distress, QoL and health status
• Prevalence and predictors of FCR in cancer survivors
• The magnitude of the interventions to reduce FCR in cancer survivors
• The level of preference of the WLC group to (optionally) complete a course of iEFT or iMMI
• The level of efficacy of both interventions between younger and older cancer survivors (< or ≥50 years)
• The level of the efficacy of both interventions between cancer survivors participating within 1 year after ending curative therapy and cancer survivors participating ≥1 year after ending curative therapy
• The time spent by iEFT and iMMI practitioners (time toxicity per patient)
Tertiary objective *
• The effect of iEFT and iMMI on chronic biological stress measured as hair cortisol concentration.

* This objective will only be completed when the primary objective is positive.

**Table 2 brainsci-15-00900-t002:** Inclusion and exclusion criteria.

Inclusion criteria
• Minimum age of 18 years at the time of enrolment
• Dutch as main language
• Histologically confirmed diagnosis of a solid cancer or haematological malignancy
• Curative surgery, chemotherapy, radiation therapy, immunotherapy, hormone therapy, targeted drug therapy or a combination of these was completed at least 2 months ago and no longer than 5 years ago at the time of enrolment. *
• Expected life expectancy of at least 5 years
• Disease-free at the time of enrolment, as defined by the absence of somatic disease activity parameters
• High FCR based on the Cancer Worry Scale 6-item version [26] (cut-off ≥ 10)
• Sufficient mental and physical functional status
Exclusion criteria
• Treatment with palliative intent
• Mental deterioration
• Organic brain syndrome (concussion without neurological symptoms and negative imaging is allowed)
• Alcohol or drug dependent
• Serious or chronic medical, neurologic or psychiatric condition that contributes to substantial physical or emotional disability that would detract from participating in either of the intervention programmes or from the measurement of intervention outcomes; a prior diagnosis of a depressive, anxiety or adjustment disorder is allowed
• Commitment to the intervention schedule is not possible
• Active practice of EFT or mindfulness (based) meditation

* Patients under current treatment for a depression or anxiety disorder are allowed to enrol, provided their depression or anxiety disorder is stable.

**Table 3 brainsci-15-00900-t003:** Overview of measures and corresponding measurement time points ^1^.

Measure	T0	T1	T2	T3
**Sociodemographic data ^2^**	X			

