### 2.5. Sample Size Calculation

The sample size calculation takes into account the principle of minimization for randomization, with participants randomized into either the iEFT group, iMMI group, or WLC group. In order to achieve at least 80% power to detect a between-group difference in mean FCRI at T1 of 10 points using an independent samples *t*-test at the two-sided 2.5% significance level (two experimental groups are compared against a single control), a total sample size of 444 patients (148 in each group) is needed, assuming a common standard deviation for FCRI in all groups of 27.9 points.

When taking into account baseline FCRI as a covariate in the regression model, the calculated sample size can be reduced by a design factor equal to (1 – r^2^) [28]. Assuming a correlation between baseline and follow-up FCRI of 0.6, the sample size reduces to 288 patients in total. This sample size has been increased to 339 patients in total to allow for an expected drop-out rate of 15%. This means we will include 113 patients in each group: iEFT (intervention), iMMI (active control), and the WLC group.

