### 2.6. Randomisation

Participants are randomised (1:1:1) to the control group (WLC) or intervention groups (iEFT or iMMI) stratified by age (< or ≥50 years), chemotherapy (yes or no), and gender (male or female). The stratified randomisation will be performed at the local sites by the site PI or his/her designee using the randomisation module of REDCap. REDCap is a secure, web-based application designed to support data capture for research studies. The REDCap software (REDCap 14.3.0) will randomise patients based on the statistical method with random permuted blocks that will be created with a computer random number generator with variable sizes to avoid the treatment allocation being predicted [27].

After randomisation, participants will be unblinded to group assignment, as the interventions do not allow for blinding. For analysis, assessor(s) and statistician(s) will be blinded.

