### 2.10. Data Analysis

All planned analyses will be performed according to the intention-to-treat principle.

Descriptive statistics will be used to describe demographic and clinical characteristics.

Clinical and psychosocial outcomes will be compared between groups using linear mixed models. Linear mixed-effects models will assess whether the improvement in FCRI scores and secondary PROMs is significantly different over time. Models will explore time x group as an interaction effect and will include the stratification variables (age, chemotherapy, and gender). Estimated marginal means with 95% confidence interval (CI) will be calculated for each time point for both groups. A 5% significance level will be used.

Within-group differences will be calculated by pairwise comparisons, enabling us to detect differences over time within the three groups. Between-group differences in the primary outcome at the primary endpoint T1 will be further examined with pairwise comparisons with T0 as the reference time point. These analyses will be repeated for the secondary PROMS: distress, QoL, and health status.

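### The time-since-therapy objective is fixed as a 1-year contrast on a 2-to-60-month interval; if the effect changes gradually, the split loses roughly 30-70% of the information

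*Protocol article*

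**What the plan says.** Table 1 of the protocol article lists, among the secondary objectives, the level of efficacy of both interventions compared between "cancer survivors participating within 1 year after ending curative therapy and cancer survivors participating ≥1 year after ending curative therapy". Table 2 requires that curative treatment "was completed at least 2 months ago and no longer than 5 years ago at the time of enrolment", so the interval can lie anywhere from 2 to 60 months.

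The article gives no reason for the 1-year boundary and no expected proportion on either side of it. Section 2.6 stratifies randomisation by age, chemotherapy and gender. Section 2.10 describes linear mixed models with a time-by-group interaction and the stratification variables. It does not describe how any subgroup objective will be modelled.

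**The concern.** Time since therapy is a continuous quantity, and Table 1 turns it into two classes. The early class covers 10 of the 58 eligible months. The late class treats a patient at 13 months and one at 59 months as alike.

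If benefit shifts gradually over survivorship, a two-class contrast uses much less of the evidence than a trend in months. If few patients enter early, the contrast also rests on a small group. At stake is whether the trial can say anything useful about when after treatment the programmes work. The main comparisons with the wait-list are not at stake.

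This is not a complaint about detail left to an analysis plan. The cut is written into the objective, and a plan that follows Table 1 would inherit it.

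**Working it through.** **Inputs from section 2.5:** SD 27.9; baseline to follow-up correlation 0.6; target difference 10 FCRI points at T1; 80% power; "two-sided 2.5% significance level"; 15% drop-out; 113 enrolled per arm. **From section 2.10:** "A 5% significance level will be used". **From Table 2:** 2 to 60 months. **Assumed, because the article gives neither:** the entry distribution over those months and the shape of any effect modification.

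**Reproducing the plan's own figures.** The normal formula gives 2 × (2.241 + 0.842)² × 27.9² / 10² = 148 per arm, 444 in total. The exact t-test gives 150 per arm; 150 × (1 − 0.36) = 96 per arm, 288 in total. Then 288 / 0.85 = 338.8, so 339. The sample size stands.

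**Precision of the 1-year contrast, even entry assumed.**
- Early share p = 10/58 = 0.172, so 96 × 0.172 = 16.55 early and 79.45 late per arm.
- Baseline-adjusted SD = 27.9 × √(1 − 0.36) = 22.32.
- SE of the difference in effect (one intervention against wait-list, early against late) = 22.32 × √(2/16.55 + 2/79.45) = 8.53.
- Detectable with 80% power at 5%: 2.80 × 8.53 = 23.9 points. At 2.5% it is 3.083 × 8.53 = 26.3.
- Power for a 10-point interaction at 5%: Φ(10/8.53 − 1.96) = 22%.

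**Same contrast at a 50:50 split.** SE = 22.32 × √(2/48 + 2/48) = 6.44. The detectable difference is about 18 points, and power for 10 points is 34%.

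**Information kept by the split.** This is the squared correlation between the 1-year indicator and time since therapy on the scale where modification is linear. For even entry and a trend linear in months it is 3p(1 − p) = 3 × 0.172 × 0.828 = 0.43, a loss of 57%. Under other assumptions:

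| Assumed entry over 2-60 months | Early share | Loss, linear in months | Loss, linear in log months |
|---|---|---|---|
| Truncated exponential, scale 6 months | 81% | 35% | 48% |
| Truncated exponential, scale 12 months | 57% | 41% | 32% |
| Truncated exponential, scale 15 months | 50% | 44% | 30% |
| Truncated exponential, scale 36 months | 30% | 51% | 30% |
| Even | 17% | 57% | 34% |
| Truncated normal, mean 24, SD 14 | 15% | 63% | 40% |
| Truncated normal, mean 30, SD 14 | 8% | 73% | 49% |

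If the effect truly steps at 1 year, the loss is zero. The range is not a bound: an entry density rising steadily towards 60 months gives 83% under the linear trend, with 3% early.

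**What a continuous term would gain, even entry and linear trend.** The early and late groups have mean times 7 and 36 months, 29 months apart. The variance of time is 58²/12 = 280.3, so its SD is 16.74. The SE of the modelled difference over 29 months is 22.32 × √(2/96) / 16.74 × 29 = 5.58, against 8.53 for the split. The detectable difference falls from 23.9 to 2.80 × 5.58 = 15.6 points, still above 10.

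**The case against.** The strongest reply is that Table 1 states an objective, not a model, and that a condensed article may leave subgroup modelling to the full protocol or analysis plan. This stands for section 2.10: the absence of a time-since-therapy term there is no fault. It does not remove the point, because the objective itself names the cut.

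A second reply is that asking whether benefit differs in the first year is a legitimate question, and that a slope answers a different one. That is fair, and it is a reason to keep the 1-year contrast as a display. No reason for 1 year is given, however, that would make it the only assessment.

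Third, low power comes from sizing the trial for main effects, and the fix does not cure it. That stands: the continuous term improves precision but leaves the objective underpowered for a 10-point difference.

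Three stronger readings are tempting but not supported:
- A reader might infer that separate tests in a small early and a large late group will produce a false message that treatment works only after 1 year. The article proposes no separate tests, and a comparison between groups is compatible with an interaction test.
- A reader might infer that the arms will be unbalanced among early patients because the interval is not a stratification factor. Randomisation balances them in expectation, and not every subgroup variable needs to be stratified.
- A reader might infer one fixed loss together with a very small early group. The loss depends on unseen assumptions, and a small early group goes with the higher losses in the linear-trend column. At a loss near 41%, the early group is the majority.

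**Conclusion.** The point holds as a minor, conditional one. Table 1 dichotomises a 2-to-60-month interval without a stated reason. If effect modification is gradual, this costs roughly 30-70% of the information on it, depending on the entry distribution and on a linear or log trend. It costs nothing if there is a true step at 1 year.

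The detectable interaction of about 24 points rests on even entry, 96 evaluable per arm, the SD and correlation of section 2.5, and a 5% level. At the most favourable split it is still about 18. That exact months are available for analysis is inferred from the eligibility rule, since the list of medical data is in a supplement not shown.

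**What to change.** In Table 1 and section 2.10, state that this objective will be assessed mainly by the interaction of group with months since end of therapy, as a continuous variable (linear or log, checked with a spline), on T1 FCRI. Use the end-of-therapy date that sites need in order to apply Table 2, and confirm that it is recorded in the study database. Report the iEFT-WLC and iMMI-WLC effects with confidence intervals at several times, for example 6, 12, 36 and 60 months. Keep the 1-year contrast as a secondary display, with its interaction estimate and confidence interval, and label the objective exploratory.

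The cost is wording plus an assumed trend shape, which the spline checks. Recruitment, sample size and the primary analysis do not change. With 82 of 339 participants at 31 July 2025 and recruitment projected to March 2027, the change could still be specified ahead of the analysis.

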**Medical data ^2^**				
**PROMs ^3^**				
Fear of Cancer Recurrence Inventory ^4^	X	X	X	X
Distress thermometer	X	X	X	X
38-item Problem List	X	X	X	X
EORTC QLQ-SURV100 ^5^	X	X	X	X
EuroQol EQ-5D-5L	X	X	X	X
**Biomarker cortisol** *	X	X		

Abbreviations: PROMs: Patient Reported Outcomes Measures; EORTC: European Organisation for Research and Treatment of Cancer; QLQ: Quality of Life Questionnaire; SURV100: survivorship questionnaire with 100 items; EuroQol: European Quality of Life. ^1^ T0: baseline (i.e., before randomisation); T1: 6 weeks after start of the iEFT or iMMI programme or 6 weeks after randomisation to the wait-list; T2: 6 weeks after end of the iEFT or iMMI programme or 12 weeks after randomisation to the wait-list; T3: 24 weeks after start of the iEFT or iMMI programme or 24 weeks after randomisation to the wait-list. ^2^ Details can be found in Supplementary Materials Section SC. ^3^ Details can be found in Supplementary Materials Section SD. ^4^ Details can be found in Appendix C. ^5^ Additionally, item 13, 14, 15, 16 and 17 of the EORTC QLQ-C30 have been added. * Optional, needs to be indicated in the Informed Consent Form (ICF).

## Appendix A. Cancer Worry Scale—6-Item Version

Please read each statement and indicate to what degree it applied to you during the past month by circling the appropriate number.

**Table A1 brainsci-15-00900-t0A1:** Cancer Worry Scale: 6-item version.

**CWS Item**				
How often have you thought about your chances of getting cancer (again)?	Hardly ever 1	Sometimes 2	Often 3	Almost always 4
Have these thoughts affected your mood?	Hardly ever 1	Sometimes 2	Often 3	Almost always 4
Have these thoughts interfered with your ability to do daily activities?	Hardly ever 1	Sometimes 2	Often 3	Almost always 4
How concerned are you about the possibility of getting cancer (again) one day?	Not at all 1	A little bit 2	Somewhat 3	Very much 4
How often do you worry about developing cancer (again)?	Hardly ever 1	Sometimes 2	Often 3	Almost always 4
How much of a problem is this worry?	Not at all 1	A little bit 2	Somewhat 3	Very much 4

## Appendix B. Content of the iMMI and iEFT Programme

**Table A2 brainsci-15-00900-t0A2:** Content of the iMMI and iEFT Programme *.

**Programme 1**	**iMMI**	**iEFT**
Session 1	**Living on automatic pilot**	**EFT basic protocol**
	Check-in, paradox of being and doing, raisin exercise, body scan, teaching: body scan, overview home practices, closing meditation and check-out	Check-in with specific questions (complaints, guidance, level of fear of cancer recurrence, expectations), teaching: tapping element, exposure element, and cognitive behavioural therapy, teaching: clinical EFT, check-out
Session 2	**Living in our head**	**Movie technique**
	Check-in, body scan, teaching: body scan, discuss home practices, teaching: obstacles and helping factors, visualisation exercise, pleasants events calendar, overview home practices, closing meditation and check-out	Check-in with specific questions (implementation of EFT in daily life, complaints, difficulties), discuss home practices, teaching: movie technique, exercise movie technique, check-out
Session 3	**Bringing the divided mind to a single point**	**Implementation of EFT**
	Check-in, teaching: postural aspects, sitting meditation with shifting focus, sitting meditation with focus on the breath, sitting meditation with focus on the body, discuss home practices, mindful movement 3 min breathing space (exercise and teaching), overview home practices, closing meditation and check-out	Check-in with specific questions (implementation of EFT in daily life, complaints, difficulties), discuss last session and home practices, personal evaluation of implementation of EFT, feedback on training and exercise plan, check-out
Session 4	**Recognizing aversion**	
	Check-in, enhanced sitting meditation, 3 min breathing space, discuss home practices, teaching: discrepancy monitor, attraction and rejection, walking meditation, teaching: stress, coping: 3 min breathing space, overview home practices, closing meditation and check-out	
Session 5	**Allowing and letting it be** Check-in, enhanced sitting meditation, exercise: 3 min breathing space, discuss home practices, coping: 3 min breathing space, teaching: theme acceptance, interim evaluation, overview home practices, closing meditation and check-out	
Session 6	**Thoughts are not facts**	
	Check-in, sitting meditation with attention for thoughts, discuss home practices, teaching: thoughts are no facts, automatic negative thoughts, personal evaluation of the training and exercise plan, closing meditation and check-out	

* As stated in 2.7, the iMMI programme contains 6 group sessions of 2 h while the iEFT programme includes three individually guided sessions that may differ in time.

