#### 2.7.1. Intervention Group—iEFT

Participants allocated to the iEFT group follow three iEFT sessions, individually guided by a clinical psychologist trained in EFT (EFT level 1 certificate acknowledged by EFT International [EFTi, Tiverton, United Kingdom]). During the trajectory, there is an in-depth initial session (±90 min) and two additional sessions (lasting ±45 and ±25 min, respectively). The duration of each session is stored in the electronic health record (i.e., measurement of time toxicity; Table 1). All sessions are guided by the iEFT practitioner on a 1:1 level.

During the first iEFT session, participants will be taught how to apply EFT and how it can be used as an application for mood and physical side effects. They will receive a digital information brochure including a section that illustrates the application of the tapping protocol. This visualisation of tapping points (Figure 2) and self-measurement scale serves as a tool to support and encourage home practice. Patients may indicate in the MyNexuzHealth app whether and when they have applied EFT. For participants who prefer a paper version of the ‘EFT diary’, it is allowed to print out the forms at home. This (digital) notebook containing a structured self-work outline will be consulted during the follow-up iEFT sessions to evaluate the previous weeks and one’s evolution throughout the iEFT trajectory.

Each session will give tools to the participants to facilitate their practice of EFT at home through formal EFT practice (together with the iEFT practitioner) as well as through guidance in the informal use of EFT during daily life. During each session, the iEFT practitioner will assist the participants in learning this practice and will regularly assess how the participants are doing with their EFT practice. An overview of the iEFT programme is presented in Appendix B.

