#### 2.7.2. Active Control Group—iMMI

The specific curriculum for this 2 h/week, 6-week programme will be provided to cancer survivors who are assigned to this group as part of the randomisation. Each session will provide structured training and exercises in mindfulness, and cancer survivors will be given tools to facilitate their practice of these techniques at home through formal meditation practice as well as through guidance in the informal use of mindfulness during daily life. During each session, the instructor will assist the participants in learning this practice and will regularly assess how the participants are doing with their mindfulness practice. All sessions are guided by a clinical psychologist who is a certified mindfulness trainer. A detailed training manual is presented in Appendix B.

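### iMMI is delivered in groups, but the 80% power for iMMI versus wait-list allows for no within-group correlation, and the listed model terms include none for session group

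*Protocol article*

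**What the plan says.** The footnote to Table A2 in Appendix B says that "the iMMI programme contains 6 group sessions" of two hours each, and sets this against three individually guided iEFT sessions. It refers back to section 2.7, but the text of section 2.7 does not say that iMMI is given in groups, so the footnote is the only place where this is explicit. Section 2.7.1 says of iEFT: "All sessions are guided by the iEFT practitioner on a 1:1 level". Section 2.7.2 says of iMMI: "All sessions are guided by a clinical psychologist who is a certified mindfulness trainer". Section 2.7.3 gives the wait-list no specific intervention before T2. The article states neither the size nor the number of iMMI groups, nor the number of trainers.

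Section 2.5 aims for "at least 80% power to detect a between-group difference in mean FCRI at T1 of 10 points", using an independent-samples t-test "at the two-sided 2.5% significance level (two experimental groups are compared against a single control"), with a common SD of 27.9. It concludes that "a total sample size of 444 patients (148 in each group) is needed". It then applies a factor for baseline correlation (r = 0.6) to reach 288, and 15% drop-out to reach 339, or 113 per arm. No ICC, group size or design effect appears.

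Section 2.10 names linear mixed models with a time-by-group interaction and says that they "will include the stratification variables (age, chemotherapy, and gender"). It does not describe the random effects.

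The comparison of iMMI with the wait-list at T1 is one of the two hypotheses in section 2.1 and one of the two primary outcome measures in section 2.9. The comparison of iEFT with iMMI is a secondary objective in Table 1.

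**The concern.** Participants in one iMMI group share six two-hour sessions, a trainer and each other's company. Their outcomes may be positively correlated for reasons that arise after randomisation, and stratifying on age, chemotherapy and gender does not remove that. Session-group clustering exists in one arm only.

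If the ICC is positive, the variance of the iMMI mean is larger than the independent-samples formula gives. Two consequences follow, and they belong to different analyses:

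- An analysis that ignores the clustering rejects too often under the null and reports intervals that are too narrow, for iMMI versus wait-list and for iEFT versus iMMI.
- An analysis that accounts for it holds its size but has less power than section 2.5 states.

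The iEFT versus wait-list contrast is not affected by session groups, so the two primary tests could differ in actual error rate or in power, although section 2.5 treats them alike.

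**Working it through.** **Inputs from section 2.5.** Difference 10; SD 27.9; two-sided alpha 2.5% (z = 2.2414); power 80% (z = 0.8416); r = 0.6; drop-out 15%.

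**Reproducing the plan's figure**

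- n per arm = 2 × [27.9 × (2.2414 + 0.8416) / 10]² = 147.98, so 148 per arm and 444 in total, as printed.
- Baseline factor 1 − 0.6² = 0.64. 444 × 0.64 = 284.2. The noncentral-t version needs 150 per arm, and 450 × 0.64 = 288, the printed figure.
- 288 / 0.85 = 338.8, so 339, or 113 per arm, as printed.

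The chain reproduces with no further factor, so the design effect in it is 1.

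**Baseline for the check.** Completers per arm: 288 / 3 = 96. Adjusted SD = 27.9 × √0.64 = 22.32. Nominal SE of a difference = 22.32 × √(2/96) = 3.222. Power without clustering = Φ(10/3.222 − 2.2414) = 80.6% (80.0% with the t distribution). There is almost no slack.

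**Adding clustering in the iMMI arm only.** Let m be the group size among completers and ICC the within-group correlation on the baseline-adjusted scale. Neither is in the document; both are assumed.

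- Design effect in iMMI: DE = 1 + (m − 1) × ICC
- True SE / nominal SE: R = √[(1 + DE)/2]
- Size of the test that ignores clustering: 2 × [1 − Φ(2.2414/R)]
- Power of that test: Φ[(3.104 − 2.2414)/R], where 3.104 = 10/3.222
- Power of a test using the true SE (size 2.5%): Φ(3.104/R − 2.2414)

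| m | ICC | DE | R | Size, ignoring clustering | Power, ignoring clustering | Power, accounting for it |
|---|---|---|---|---|---|---|
| 4 | 0.01 | 1.03 | 1.007 | 2.6% | 80.4% | 79.9% |
| 4 | 0.05 | 1.15 | 1.037 | 3.1% | 79.7% | 77.4% |
| 8 | 0.05 | 1.35 | 1.084 | 3.9% | 78.7% | 73.3% |
| 10 | 0.05 | 1.45 | 1.107 | 4.3% | 78.2% | 71.3% |
| 12 | 0.05 | 1.55 | 1.129 | 4.7% | 77.8% | 69.4% |
| 12 | 0.10 | 2.10 | 1.245 | 7.2% | 75.6% | 59.9% |

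**One line in full (m = 10, ICC 0.05).** DE = 1 + 9 × 0.05 = 1.45. R = √(2.45/2) = 1.107. The true SE is 11% larger than the nominal SE; equivalently, the nominal SE is 1 − 1/1.107 = about 10% too small. Size = 2 × [1 − Φ(2.2414/1.107)] = 4.3%. Power ignoring clustering = Φ(0.863/1.107) = 78%. Power accounting for it = Φ(3.104/1.107 − 2.2414) = 71%.

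The same factor R applies to iEFT versus iMMI if iEFT is unclustered. These are normal approximations. With 96 completers there are only 96/12 = 8 to 96/4 = 24 groups, so a test with small-sample degrees of freedom would have somewhat less power than the last column shows.

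**The case against.** The strongest reply concerns the model. Section 2.10 describes no random effects, not even the participant effect that a repeated-measures mixed model would normally carry, so its list of terms is not exhaustive. A condensed article commonly leaves the random-effects structure and degrees of freedom to the full protocol or SAP, and neither is shown. This stands. A reader might infer that the planned analysis treats iMMI participants as independent and that its standard errors are therefore wrong. The article does not establish that; it shows only that no session-group term is among those listed. The reply does not reach section 2.5, where the independence assumption is part of a printed calculation.

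Second, a reader might pair an inflated type I error of 4.3% with a power of 71%, as if one test had both. It does not: 4.3% goes with 78% (clustering ignored), and 71% goes with 2.5% (clustering accounted for).

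Third, the size depends on two quantities that the article does not give. Accrual hints that groups may be small: 82 participants were randomised between 16 October 2024 and 31 July 2025, about 9.5 months, which is 82 / 3 / 9.5 = about 3 iMMI participants per month. Larger groups would need several months of recruits pooled. This also stands, and it is why the range above starts at m = 4, where an ICC of 0.01 makes the effect negligible.

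Finally, the eCRF variables are listed in a supplement that is not shown, so it cannot be said that the session-group identifier goes unrecorded.

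**Conclusion.** The point holds in two parts of different strength.

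The sample-size part is firm. The power for the primary iMMI versus wait-list contrast was computed as if iMMI were delivered individually, and with 96 completers per arm there is practically no reserve to absorb any positive ICC.

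The model part is conditional. If no fuller plan contains a session-group effect, standard errors for iMMI versus wait-list and iEFT versus iMMI are too small whenever the ICC is positive.

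Across assumed sizes 4 to 12 and ICC 0.01 to 0.10, the consequence is either a true size of 2.6% to 7.2% at nominal 2.5% with power about 80% to 76%, or a held size with power about 80% to 60%. The documents do not support calling the trial seriously underpowered: the low end of the range is negligible, and nothing in the article places the trial within it. Confidence is high on the sample-size assumption and moderate on the size of the effect. The iEFT versus wait-list contrast is outside this point, and any clustering by iEFT practitioner would be a separate question.

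**What to change.** 1. Make sure the iMMI session-group identifier is recorded for every iMMI participant. With 82 of 339 randomised by 31 July 2025, most of it can be captured prospectively; earlier groups should be recoverable from session schedules if it is not already held.
2. In section 2.10, specify a random effect for session group that applies to the iMMI arm only, with arm-specific residual variance and Satterthwaite or Kenward-Roger degrees of freedom. If a fuller plan already has this, confirming it is enough.
3. In section 2.5, state the planned iMMI group size and restate the power for iMMI versus wait-list over a range of ICCs, leaving N unchanged.

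The cost is at most one data field, one model term and a short revision of the power statement. The downside is real: intervals for the iMMI contrasts will be wider, and the stated power for one of the two primary comparisons will be lower, for example 71% rather than 80% at group size 10 and ICC 0.05.
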